**Methods:**

Participants are recruited from GP referrals in an urban setting, from a neurosurgery non-urgent waiting list and from self-referral through Facebook advertising. Eligible participants (*n* = 64) are diagnosed with radiculopathy based on a clinical prediction rule and must have symptoms of unilateral, single level, radiculopathy for between 2 and 12 weeks, without having yet received physiotherapy. Random 1:1 group allocation (using variable block sizes), allocation concealment, blinded assessment and intention to treat analysis are being employed. Treatment is provided by clinical specialist physiotherapists in primary and secondary care settings. Outcomes are measured at baseline, 4 (primary endpoint) and 12 weeks. Participants’ report of pain, disability and their rating of recovery is also recorded by telephone interview at 6 months. Statistical analysis of between group differences will be performed with ANOVAs and MANOVAs, and multivariable regression analysis will be undertaken to explore predictor variables. Ethical approval for this study has been received from the Beaumont Hospital and Irish College of General Practitioners Research Ethics Committees. The trial is registered at ClinicalTrials.gov (NCT02449200).

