## Methods

### Study design

The PACeR trial is an exploratory, two parallel group, assessor-blinded, multi-centre randomised controlled trial, with a primary endpoint of pain and disability at 4 weeks. This is a superiority trial to investigate a novel, complex physiotherapy intervention using allocation concealment, blocked randomisation and a 1:1 allocation ratio. The SPIRIT statement and CONSORT guidelines are guiding the reporting and conduct of the study [24, 25]. Ethical approval for this study has been granted by the medical research ethics committees of Beaumont Hospital (REC ref. 14/85), the Irish College of General Practitioners (ICGP) and the Royal College of Surgeons in Ireland (RCSI). Recruitment is via GP referral, self-referral through social media advertising, and initially, also from a waiting list of non-urgent referrals to a national neurosurgery centre. Five clinical centres (1 hospital and 4 private practices) are currently providing the trial’s interventions. Physiotherapy is provided by postgraduate master’s level or clinical specialist musculoskeletal physiotherapists.

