### Sample size estimation

The NDI and the NPRS are the independent primary outcome measures and sample size estimates were carried out for both outcome measures. An MCID for the NDI of 7 has been determined for cervical radiculopathy [48]. Using a reported NDI SD of 9.2 [48] for this patient group, with a two-sided 5% significance level and a power of 80%, a sample size of 29 participants per group is necessary. An MCID for the NPRS of 2 has been determined for mechanical neck pain, including cervical radiculopathy [43] and a SD of 1.85 [48]. Using these figures, with a two-sided 5% significance level and a power of 80%, a sample size of 15 per group was calculated. An online sample size calculator [49] for comparing means of 2 independent groups, that utilises reference tables [50] was used. The larger sample size per group calculated using the NDI was chosen and an additional 10% was added to account for anticipated dropout. In total, a sample size of 64 participants will be recruited.

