### Data analysis plan

Baseline demographic characteristics and all outcome measures will be described and analysed using SPSS (IBM, version 24) or Stata statistical software (Statacorp LLC, Release 15). Descriptive characteristics will be presented for both groups following the CONSORT Statement. Data will be checked for normality using the Shapiro-Wilk test. Marginal effects will be used to calculate effect sizes for specified values for baseline differences. Results will be reported as mean differences between the groups and their 95% confidence intervals. Poisson regression will be used where data are non-parametric (Bland and Altman, 2011).

Statistical analysis will include two-way (treatment x time) ANOVAs and MANOVAs for between and within-group differences and interactions. Intention to treat analysis will be the primary approach employed. A per protocol analysis will also be undertaken and results compared to assess the impact of data that is not missing at random (NMAR) (Armijo-Olivo et al., 2009).

Secondary analysis will explore if any of the baseline outcome measures, symptom duration and group allocation are predictors of outcome (pain and disability) at 3 months. Appropriate multivariable regression analysis will be performed (linear or logistic).

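### The treatment x time ANOVA/MANOVA is not tied to the 4-week group difference on which the trial is sized; a baseline-adjusted 4-week contrast should be named as primary

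*Protocol article*

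**What the plan says.** The Study design section describes a trial "with a primary endpoint of pain and disability at 4 weeks". The abstract agrees: "Outcomes are measured at baseline, 4 (primary endpoint) and 12 weeks". The Sample size estimation section uses a calculator "for comparing means of 2 independent groups". For the NDI its inputs are "An MCID for the NDI of 7 has been determined for cervical radiculopathy" and "Using a reported NDI SD of 9.2", and it concludes "with a two-sided 5% significance level and a power of 80%, a sample size of 29 participants per group is necessary".

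The Data analysis plan then states: "Statistical analysis will include two-way (treatment x time) ANOVAs and MANOVAs for between and within-group differences and interactions". The abstract likewise gives ANOVAs and MANOVAs as the method for between-group differences. The Data analysis plan also promises group mean differences with 95% confidence intervals, marginal effects evaluated at chosen baseline differences, and Poisson regression for data it calls non-parametric. It adds: "Intention to treat analysis will be the primary approach employed". None of these statements names the visits that enter the model, the term that decides the trial, or the 4-week contrast.

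**The concern.** The endpoint and the sample size concern one contrast: the difference between groups at 4 weeks. A treatment x time ANOVA yields several tests, and they answer different questions.

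- **Group main effect.** This is the group difference averaged over the visits in the model. If baseline is one of them, it contributes an expected difference of zero, because it precedes randomisation. The estimate is pulled towards zero.
- **Omnibus interaction.** With three visits this is a 2-df test of any difference in time profile. A significant result need not concern week 4 and gives no 4-week estimate.
- **Interaction with baseline and week 4 only.** This is the group difference in change. It targets the right quantity, but it does not use the baseline score as efficiently as regression adjustment does.
- **Within-group tests.** These cannot separate treatment from natural recovery, which the Background describes as favourable.

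If the deciding term is left open, the estimate, its precision and the chance of a positive result depend on a choice that could be made after the data are seen.

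**Working it through.** **Inputs from the protocol (Sample size estimation).** NDI difference 7, SD 9.2, two-sided 5%, 80% power, 29 per group, 10% added for dropout, total 64.

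**Assumptions not in the protocol.** Equal variances and one common correlation r between visits (0.3 to 0.7); a true 12-week difference of 7, 3.5 or 0; 9.2 read as the SD of raw scores.

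**Step 1: the plan's own figure.** n = 2 × [9.2 × (1.960 + 0.842) / 7]² = 27.1, so 28 by the normal approximation. The t-based solution is 28.1, so 29 per group. Then 29 × 1.10 = 31.9, so 32 per group and 64 in total. The plan's figure is reproduced. An unadjusted t-test at 4 weeks with 29 per group has 81.3% power.

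**Step 2: group main effect over three visits.** Estimate = (0 + 7 + d12) / 3, where d12 is the 12-week difference. The variance of a participant's mean is 9.2² × (1 + 2r) / 3. At r = 0.5 this is 84.64 × 2/3 = 56.4 (SD 7.51), so the standard error of the group difference is 7.51 × √(2/29) = 1.97.

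| 12-week difference | Main effect estimates | Power, r = 0.5 | Power, r = 0.3 to 0.7 |
|---|---|---|---|
| 7 | 4.67 | 64.2% | 73.9% to 56.5% |
| 3.5 | 3.50 | 41.5% | 49.6% to 35.7% |
| 0 | 2.33 | 21.4% | 25.5% to 18.6% |

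With baseline and week 4 only, the main effect estimates 3.5 points, with 42.3% to 33.9% power.

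**Step 3: omnibus interaction, three visits.** Noncentrality = (29/2) × Σ(d − mean d)² / [9.2² × (1 − r)], on 2 and 112 df. For differences (0, 7, 7) the sum of squares is 32.67, so at r = 0.5 the noncentrality is 14.5 × 32.67 / 42.32 = 11.2. The differences (0, 7, 0) give the same sum.

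| 12-week difference | r = 0.3 | r = 0.5 | r = 0.7 |
|---|---|---|---|
| 7 or 0 | 70.5% | 84.9% | 97.6% |
| 3.5 | 57.2% | 72.7% | 92.1% |

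The test has the same power whether the effect is sustained at 12 weeks or gone, which shows that it is not a statement about week 4.

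**Step 4: contrasts that do target the 4-week difference of 7.** Change-score SD = 9.2 × √[2(1 − r)]. Baseline-adjusted (ANCOVA) SD = 9.2 × √(1 − r²).

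| 4-week contrast | r = 0.3 | r = 0.5 | r = 0.7 |
|---|---|---|---|
| Difference in change | 67.2% | 81.3% | 95.7% |
| Baseline-adjusted | 84.7% | 90.8% | 97.9% |

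At r = 0.5 the change-score SD is 9.2 and the adjusted SD is 9.2 × √0.75 = 7.97. The 95% CI half-widths are about 2.00 × 9.2 × √(2/29) = 4.8 points and 2.00 × 7.97 × √(2/29) = 4.2 points.

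**The case against.** A reader might infer that the planned analysis cannot estimate the 4-week effect at all. The protocol does not support that. A treatment x time model contains a 4-week contrast, and with baseline and week 4 only its interaction is the difference in change, which is unbiased under randomisation. The section does not make the main effect the deciding test or say which visits enter. Its wording is not exclusive, and its promised mean differences and marginal effects point towards some baseline-conditional estimate. This stands, so the low powers in Step 2 describe one term that could be chosen, not what the plan will do.

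A reader might also infer that the stated 80% power is wrong. That is not shown. The sample size is correct for the comparison it describes, and the omnibus interaction exceeds 80% in some scenarios. The protocol does not say whether 9.2 is a raw-score or a change-score SD. If it is a change-score SD, the change contrast has about 81% power whatever r is.

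A third inference is that anyone who misses week 12 is dropped from the primary analysis. Listwise deletion is how these procedures usually behave, but the protocol does not state it, and it makes intention to treat primary. Nor does the protocol use within-group tests as evidence of efficacy; its null hypothesis is between groups.

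Finally, a full analysis plan could name the contrast, and its absence from an article is no fault in itself. But the article does state a method. A better one, using data already collected, can replace it at no cost, so the recommendation does not rest on missing detail.

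**Conclusion.** The point holds in a limited form. The named analysis is not tied to the 4-week difference that defines the endpoint and the sample size, and two of its natural tests do not target that difference. With 29 per group, the main effect would shrink a true 7-point effect to between 2.3 and 4.7 points, and the omnibus interaction gives no 4-week estimate. The change contrast is valid, but it has less power than baseline adjustment by about 18 percentage points at r = 0.3, 10 at r = 0.5 and 2 at r = 0.7.

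Baseline adjustment had more power than every ANOVA term in every scenario computed. The margin runs from under 1 percentage point (omnibus interaction, r = 0.7, 12-week difference 7 or 0) to over 70 (main effect, r = 0.7, 12-week difference 0). The sizes rest on the assumed r, the assumed 12-week effect, equal variances and a raw-score SD of 9.2. The direction of the recommendation does not depend on one particular value within those ranges. The sample size needs no change.

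**What to change.** State in the Data analysis plan that the primary analysis of each primary outcome (NDI, and NPRS for neck and arm pain) is the baseline-adjusted difference between groups at 4 weeks, with its 95% CI. Obtain it in one of two ways:

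- ANCOVA of the 4-week score on group and baseline score; or
- a linear mixed model for the 4- and 12-week scores with group, time, group x time and baseline x time, which keeps all randomised participants with any follow-up. The primary estimate is its 4-week group contrast.

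Describe the group main effect, the omnibus interaction and the within-group tests as descriptive. Adjustment for symptom duration is optional, since the randomisation is blocked with no stratification described.

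The cost is wording only. SPSS and Stata, both already named, fit either model, and the baseline, 4- and 12-week scores are already collected. The wording should be settled before outcomes are compared between groups.

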### Aims

The trial’s primary aim is to investigate the effects of a multimodal physiotherapy (MP) programme on the independent primary outcome measures of disability, using the Neck Disability Index [13]; and pain, using the NPRS for both neck and arm pain at 4 weeks [14].

Secondary aims are;

To investigate the effects of the MP programme on selected biopsychosocial outcome measures at 4 and 12 weeks;I.Patient reported outcome measures -◦ Health-related quality of life using the SF-12 version 2 Health Survey [15].◦ Mood using the Hospital Anxiety Depression Scale (HADS) [16].◦ Fear avoidance using the Fear Avoidance Belief Questionnaire (FABQ) Neck [17, 18]. ◦ Patient rating of recovery using the Global Rating of Change scale [19].II.Clinical physical examination measures -◦ Cervical range of motion measured with a CROM 3 device (Performance Attainment Associates, USA). Flexion, extension, bilateral side flexion and rotation are being measured.◦ Pressure pain threshold (PPT) measured with pressure algometry [20], and the Upper Limb Neurodynamic Test (ULNT) 1 [21, 22] as measures of nerve mechanosensitivity.To identify whether any of the biopsychosocial outcome measures, as well as PainDETECT [23] at baseline, symptom duration and group allocation; can predict outcome (pain and disability) at 3 months.

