### Eligibility criteria

Adults with single-level cervical radiculopathy of less than 12 weeks duration are eligible to participate. Inclusion & exclusion criteria are adapted from studies of similar cohorts [26, 27].

Inclusion criteria:Participants aged 18 years or older.Meet criteria for CR diagnosis on a clinical prediction rule (CPR) by demonstrating positive responses to at least 3 of the following clinical tests: Spurling’s Test, Upper Limb Neural Tissue Provocation Test 1 (ULNT 1), Cervical Distraction Test, and cervical rotation (less than 60°) on the symptomatic side [28].Complains of neck or periscapular pain in addition to radicular pain, paraesthesia or numbness in the upper limb; aggravated by neck posture or movement [29].Symptom duration must be greater than 2 weeks and less than 3 months.Mean of Numerical Pain Rating Scale (NPRS) scores for both neck and arm pain must be ≥3/10.Fluent in spoken & written English.

Exclusion criteria:Previous physiotherapy or manual treatment to cervical spine within past 6 months.Previous epidural injection since the onset of current symptoms.Prior surgery to the cervicothoracic spine or currently symptomatic upper limb.Current bilateral upper-limb symptoms.Myotomal paresis less than 4/5 on Medical Research Council (MRC) Scale in affected upper limb.Signs and symptoms suggestive of Cervical Spondylotic Myelopathy (CSM): bilateral paraesthesia, hyperreflexia, positive Babinski reflex and spasticity.Diagnosis of any generalised neurological disorder e.g. multiple sclerosis.Concurrent peripheral neuropathy affecting either upper limb e.g. carpal tunnel syndrome, thoracic outlet syndrome.Medical red flags suggestive of serious pathology such as neoplastic conditions, upper cervical ligamentous instability, vertebral artery insufficiency and inflammatory orsystemic disease [30].Diagnosis of fibromyalgia.Psychiatric diagnosis in past 6 months.Ongoing litigation relating to cervical symptoms.

A two-step screening process is used to determine eligibility. A successful phone screen is followed by physical examination. Physical exam includes a neurological exam and manual exam of the cervical spine (C2-T2) to identify the symptomatic nerve root level.

If an MRI of the patient’s cervical spine has been undertaken, the report is reviewed for concordance after the initial assessment.

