**Table 1 Tab1:**
[figure not shown]
PACeR trial schedule of enrolment, interventions, and assessments adapted from original table© SPIRIT Group [48]

A CPR with established diagnostic accuracy is used to confirm the presence of CR [28]. This involves 4 physical tests, which include measurement of cervical rotation and Upper Limb Neurodynamic Test (ULNT) 1. Cervical rotation range is measured with a CROM 3 device (Performance Attainment Associates, USA) made up of 3 cervical inclinometers. Reliability (ICC = 0.89–0.90) and construct validity of the CROM have been demonstrated [38]. ULNT 1 is a validated pain provocation test for nerve tissue [21, 22], which has also demonstrated moderate reliability (kappa = 0.45) [39].

Participants undergo the following outcome measures at baseline, 4 and 12 weeks:

The *Neck Disability Index* is a ten-item self-reported questionnaire that assesses pain and associated disability [13]. The NDI is valid and reliable for use in cervical radiculopathy [40]. The Taskforce on Neck Pain considered it to be the most responsive self-assessment questionnaire available [41] due to its ability to discriminate between clinical improvement and deterioration in neck pain [42].

The *Numerical Pain Rating Scale,* a reliable and responsive [43] generic measure of pain [14] is being used to measure both neck and arm pain.

Cervical *range of motion* measured with a CROM 3 device (Performance Attainment Associates, USA). Flexion, extension, side flexion and rotation, along with symptom response, is being measured.

The *SF-12 Health Survey* questionnaire will be used as a measure of quality of life (QoL) and is a practical, reliable, and valid measure of physical and mental health [44, 45].

The *Hospital Anxiety and Depression Scale (HADS)* and the *Fear Avoidance Belief Questionnaire (FABQ)* are used as psychosocial measures. The HADS [16] was developed as a tool to identify anxiety and depression in patients attending non-psychiatric hospital outpatient clinics and has been validated [46]. The FABQ was initially established to measure how patients’ beliefs about physical activity and work affected their low back pain [17]. FABQ has also been shown to predict prolonged disability in neck pain patients, making it appropriate to use with this cohort of neck pain patients [18].

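### Within-group significance tests are planned on measures that also decide entry (ULNT 1, symptomatic-side rotation, NPRS); their p-values lean toward improvement, materially only for ULNT 1, and the randomised comparison is unaffected

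*Protocol article*

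**What the plan says.** **Entry.** Under Eligibility criteria, participants qualify "by demonstrating positive responses to at least 3 of the following clinical tests". Two of the four tests are ULNT 1 and "cervical rotation (less than 60°) on the symptomatic side". At most one test can be negative, so every entrant is abnormal on at least one of these two. A further criterion reads "Mean of Numerical Pain Rating Scale (NPRS) scores for both neck and arm pain must be ≥3/10".

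**Outcomes.** The Aims list "pain, using the NPRS for both neck and arm pain at 4 weeks" as a primary outcome. Cervical rotation is a secondary outcome at 4 and 12 weeks, and so is ULNT 1: "and the Upper Limb Neurodynamic Test (ULNT) 1 [21, 22] as measures of nerve mechanosensitivity".

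**Reliability.** Under Outcome measures, ULNT 1 is described as a test "which has also demonstrated moderate reliability (kappa = 0.45"; the CROM device is given an ICC of 0.89-0.90.

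**Analysis.** The Data analysis plan commits to this: "Statistical analysis will include two-way (treatment x time) ANOVAs and MANOVAs for between and within-group differences and interactions". It makes no exception for measures used for selection. The paragraph before it says that results will be given as between-group mean differences with 95% confidence intervals.

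**The concern.** Someone admitted partly because a reading was abnormal will, on average, read somewhat less abnormal at the next measurement even if nothing has changed. A within-arm test from that baseline counts this shift as improvement. The main effect of time in a treatment-by-time ANOVA pools the two arms and carries the same shift. Natural recovery, which the Background describes as favourable, pushes the same way and also affects NDI, although NDI is not an entry criterion.

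What is at stake is how secondary results read. With 29 evaluable participants per arm, a sample sized on NDI and NPRS, a null between-group result on ULNT 1 could stand beside a significant within-arm p-value that owes nothing to treatment.

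**Working it through.** **The plan's own figures.** The article gives no figure for this artefact. The arm size used below does reproduce. A two-sample t-test at 80% power and two-sided 5% gives 28.1, so 29 per group, for NDI (difference 7, SD 9.2), and 14.5, so 15, for NPRS (difference 2, SD 1.85). Then 58 × 1.10 = 63.8, so 64.

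**Inputs from the article:** 3-of-4 rule; rotation cut 60 degrees; mean NPRS cut 3; kappa 0.45; ICC 0.89-0.90; NPRS SD 1.85; n = 29 per arm.

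**Assumed, shown as ranges:** ULNT 1 positivity p among those screened, 0.3-0.7; other tests independent of it and 60% positive each; rotation mean 50-70 degrees, SD 10-15; NPRS mean 3-6, reliability 0.6-0.9; qualifying reading used as baseline; ULNT 1 scored positive or negative; no treatment effect and no recovery.

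**ULNT 1, proportion positive at entry.** A ULNT-positive person needs at least 2 of the other 3 tests: 3 × 0.6² × 0.4 + 0.6³ = 0.648. A ULNT-negative person needs all 3: 0.6³ = 0.216. Hence π = 0.648p / [0.648p + 0.216(1 − p)].

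**ULNT 1, change on repeat.** A positive turns negative with probability (1 − p)(1 − κ), and a negative turns positive with probability p(1 − κ). The net fall is therefore π(1 − p)(1 − κ) − (1 − π)p(1 − κ) = (π − p)(1 − κ).

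| p | π at entry | fall at κ = 0.45 | exact McNemar rejection, n = 29 |
|---|---|---|---|
| 0.3 | 0.56 | (0.5625 − 0.3) × 0.55 = 14.4 points | about 19% |
| 0.5 | 0.75 | (0.75 − 0.5) × 0.55 = 13.8 points | about 17% |
| 0.7 | 0.875 | (0.875 − 0.7) × 0.55 = 9.6 points | about 8% |

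The rejection rates were simulated from these transition probabilities. A second simulation passed rotation through its own 60-degree cut (p = 0.5 or 0.7, rotation mean 50 or 60, SD 12) and used a paired t-test on the 0/1 score. At κ = 0.45 it gave falls of 9-15 points and rejection in 17-32% of arms. At κ = 0.8 and p = 0.5 the fall is (0.75 − 0.5) × 0.20 = 5 points, and rejection is about 10% with the paired t-test and about 1% with the exact test.

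**Rotation and NPRS.** Expected shift = (1 − r) × SD × φ(a)/tail(a), where a = (cut − mean)/SD.

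- Rotation, worst case (mean 70, SD 15, r = 0.89, cut binding on everyone): a = −0.667, ratio 1.265, shift 0.11 × 15 × 1.265 = 2.1 degrees. Across the grid the shift is 0.3-2.1 degrees. Under the actual 3-of-4 rule it is 0.3-0.55 degrees, with within-arm rejection of 5-8%.
- NPRS, worst case (mean 3, r = 0.6): a = 0, ratio 0.798, shift 0.4 × 1.85 × 0.798 = 0.59 points, with rejection of about 46%. At mean 5 and r = 0.75 the shift is 0.12 points, with rejection of about 8%.

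**Between groups.** In the same simulations the between-group test rejected in 4.5-5.3% of trials for all three measures, as it should.

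**The case against.** The strongest reply is that the plan already does most of what is asked. The null hypothesis is a between-group one, results are to be reported as between-group differences with confidence intervals, and the sentence in question also names the interaction. All of that stands, and it keeps this point minor. It does not remove the commitment in the same sentence to test within-group differences.

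Three premises are not in the article: that the qualifying reading is the baseline, that ULNT 1 is analysed as positive or negative, and that the quoted kappa describes repeat testing by the same assessor. The investigator's own intra-rater reliability is still to be verified. A separate pre-treatment reading would largely remove the selection artefact, and a higher kappa would shrink it. Natural recovery would remain.

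A reader might infer that the plan intends to present change in the control arm as natural history, because the Abstract calls the short-term course somewhat unclear. Nothing in the article says so, and estimating natural history is not among the Aims.

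**Conclusion.** The point holds as a minor correction confined to the within-group tests. Entry criteria and outcomes overlap, within-group testing is stated, and the expected drift is toward improvement in both arms. For ULNT 1 it is about 9-15 percentage points at kappa 0.45, with a significant change in about 8-32% of arms depending on the test and the assumed screening positivity. For rotation it is usually under 1 degree, and for NPRS at most about 0.6 points. All of this is conditional on the assumptions listed above.

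Three stronger readings are tempting and not supported:

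- That both arms will appear improved on all three measures through selection alone. Rotation and NPRS shift little. Neither ULNT 1 nor rotation is individually required, and the NPRS cut applies to the mean of neck and arm, which weakens truncation of each score.
- That within-arm ULNT 1 tests would be falsely significant in 38-68% of cases. This needs 85-95% ULNT 1 positivity at entry with 50% at screening. The 3-of-4 rule guarantees 75% only as an average over the four tests and, with the independent tests assumed here, gives about 75% for ULNT 1 at that prevalence.
- That the trial's main result is biased. The artefact is the same in both arms and cancels in the randomised contrast.

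**What to change.** In the Data analysis plan, remove within-group differences from the list of tested effects, for all outcomes including NDI. Report change from baseline in each arm descriptively (mean and SD, or number and percentage positive) without p-values. State that every efficacy conclusion rests on the between-group contrast, or the treatment-by-time interaction, at 4 and 12 weeks with its 95% confidence interval, and that the main effect of time is not read as a treatment effect.

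The cost is wording only: no new data, visits or participants. The downside is that the report can make no within-group significance statements.

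### The only between-group test named, a two-way treatment x time ANOVA/MANOVA, is not tied to the 4-week primary endpoint or to the comparison that was powered

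*Protocol article*

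**What the plan says.** - **Endpoint.** Under Study design the trial is described "with a primary endpoint of pain and disability at 4 weeks". The abstract's Methods agree: "Outcomes are measured at baseline, 4 (primary endpoint) and 12 weeks". The Aims also place disability (NDI) and neck and arm pain (NPRS) at 4 weeks.
- **Sample size.** Sample size estimation uses a calculator "for comparing means of 2 independent groups", with an NDI difference of 7, SD 9.2, two-sided 5% and 80% power, giving 29 per group. The section does not restate the visit.
- **Visits.** Under Outcome measures: "Participants undergo the following outcome measures at baseline, 4 and 12 weeks". NDI and NPRS are collected again by phone at 6 months.
- **Test.** The abstract says: "Statistical analysis of between group differences will be performed with ANOVAs and MANOVAs". The Data analysis plan makes this specific: "Statistical analysis will include two-way (treatment x time) ANOVAs and MANOVAs for between and within-group differences and interactions".
- **Estimates.** The same section adds: "Results will be reported as mean differences between the groups and their 95% confidence intervals". It also says: "Marginal effects will be used to calculate effect sizes for specified values for baseline differences". Neither sentence gives a visit.
- **Other methods named.** Poisson regression is the fallback for data judged non-parametric. Multivariable regression is for predicting the 3-month outcome.

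**The concern.** A treatment x time ANOVA yields a group main effect, a time effect and an interaction. With more than two visits, neither of the terms involving treatment is the difference at one chosen visit. The main effect averages the group difference over all visits, including baseline, where randomisation makes its expectation zero. The interaction asks whether the difference varies across visits in any way, so a difference at 12 weeks alone can make it significant. A MANOVA is a further omnibus test. If it is taken across outcomes, it gives no separate answer for NDI or NPRS, which the article treats as separate primary outcomes.

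The text therefore leaves open which visits and which term answer the 4-week question. Different choices can give different answers from the same data, and the stated 80% power belongs to only one of them.

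**Working it through.** **1. Reproduce the plan's figures.** The exact two-sample t-test calculation gives 28.11, so 29 per group (NDI: difference 7, SD 9.2), and 14.46, so 15 per group (NPRS: difference 2, SD 1.85). Adding 10% gives 58 x 1.10 = 63.8, so 64. All three match the article. At 29 per group the standard error of a 4-week difference is 9.2 x sqrt(2/29) = 2.416, and power for 7 points is 81.3%.

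**2. Assumptions not in the document.** The model uses three visits (baseline, 4 and 12 weeks). SD is 9.2 at every visit. The correlation r between any two visits is equal, at 0.3, 0.5 or 0.7. Baseline difference is zero. Results below are in the order r = 0.3 / 0.5 / 0.7.

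**3. Group main effect.** The quantity tested is the mean of the three visit differences, with standard error 9.2 x sqrt[((1+2r)/3) x (2/29)] = 1.764 / 1.973 / 2.161 on 56 df.
- 7 points at both follow-ups: (0+7+7)/3 = 4.67. Power 73.9% / 64.2% / 56.5%.
- 7 points at one follow-up only: (0+7+0)/3 = 2.33. Power 25.5% / 21.4% / 18.6%.

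**4. Interaction, F on 2 and 112 df.** The noncentrality is (29/2) x (sum of squared centred visit differences) / [9.2² x (1−r)]. For differences (0,7,7), (0,7,0) and (0,0,7) the sum of squares is the same, 32.67. The noncentrality is therefore 8.00 / 11.19 / 18.65, and the rejection rate is 70.5% / 84.9% / 97.6% in all three cases.

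**5. Side by side.**

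| True NDI difference at 4 and 12 weeks | Main effect | Interaction | 4-week t-test |
|---|---|---|---|
| 0 and 7 | 26 / 21 / 19% | 71 / 85 / 98% | 5% |
| 7 and 0 | 26 / 21 / 19% | 71 / 85 / 98% | 81% |
| 7 and 7 | 74 / 64 / 57% | 71 / 85 / 98% | 81% |

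A simulation with 10,000 trials per scenario agrees to within about one percentage point. It also covered a benefit of 7 at 4 weeks falling to 3.5 at 12 weeks: main effect 50 / 42 / 34%, interaction 56 / 73 / 92%.

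**6. If only baseline and 4 weeks enter.** The interaction is then exactly a t-test on 4-week change, with standard error 9.2 x sqrt[2(1−r) x (2/29)] = 2.859 / 2.416 / 1.871 and power 67 / 81 / 96%. This does test the 4-week question.

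**7. Baseline-adjusted 4-week comparison.** The standard error is about 9.2 x sqrt[(1−r²) x (2/29)] = 2.305 / 2.092 / 1.725 on 55 df, and power is about 85 / 91 / 98%. With no 4-week effect it rejects about 5% of the time, whatever happens at 12 weeks.

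**The case against.** The strongest reply is that the article never says an omnibus term decides the trial. In the Data analysis plan, the word primary is attached to intention to treat, not to the ANOVA, and the ANOVAs are only among the things the analysis will include. The time levels are not given, so the three-visit model is the reader's assumption. Mean differences with 95% CIs are promised. The marginal-effects sentence suggests estimates from a baseline-adjusted model, and the 4-week endpoint is fixed elsewhere. Read together, a 4-week mean difference with its CI is a natural reading. A full protocol or SAP that is not shown may say exactly that.

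Much of this stands. A reader might infer that the plan names the omnibus ANOVA as its primary method, or that the method cannot test the 4-week difference. The text supports neither: with two visits the interaction is the 4-week comparison of change, and a 4-week contrast can be read from a larger model. A reader might also infer a general loss of power. That is not so either, because the interaction has 71 / 85 / 98% power for a 7-point 4-week effect, whether or not it persists unchanged to 12 weeks. The 12-week-only scenario is extreme, although participants in the physiotherapy arm are advised to keep exercising until the 12-week assessment.

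What the reply does not remove is the mismatch in what is stated. The article does commit to a test in both the abstract and the Data analysis plan. It is a different kind of test from the one powered, and no sentence links it to 4 weeks.

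**Conclusion.** The point holds as a failure to tie the named test to the endpoint; it does not show that the analysis is wrong. Under the three-visit assumption, with 29 per group, SD 9.2 and equal correlation of 0.3 to 0.7, two consequences follow:

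- The interaction would reject in about 71% to 98% of trials with no 4-week effect and a 7-point effect at 12 weeks.
- The main effect would have 57% to 74% power for a sustained 7-point effect and 19% to 26% for one present at 4 weeks only, against 81% for a direct 4-week comparison.

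The first concerns only the interaction as a decision rule and the second mainly the main effect. Neither arises if the model is confined to baseline and 4 weeks and the interaction decides, or if a 4-week contrast is taken. The sample-size figures are correct for the comparison they describe. The change is worth making because it is cheap and closes a choice that could otherwise be made after the data are seen, but the validity of the trial does not depend on it.

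**What to change.** State in the Data analysis plan, and consistently in the abstract:

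- For each primary outcome the deciding result is the between-group mean difference at 4 weeks with its 95% CI. It comes either from a linear model of the 4-week score adjusted for baseline, or as the 4-week contrast of a repeated-measures model with a separate treatment effect at each follow-up visit.
- The 12-week difference is a secondary contrast.
- The group main effect, the omnibus interaction and any MANOVA are descriptive and do not decide the primary conclusion.

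If an SAP already says this, the article's wording should be brought into line with it. The cost is analysis wording only, with no new participants, visits or data. Under the assumptions above, baseline adjustment raises power from 81% to about 85 / 91 / 98%.
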